### Procedure

As both PLA and INT are the interventions, they will follow the same protocol for ingestion: 5 g per day for 7 weeks. All 5 g will be ingested at once (9). This protocol has been chosen instead of the more common 0.3 g/day for the first week ingested five times during the day (9). In other studies on CrM and the brain, 5 g per day was also the chosen strategy (31, 32). However, studies on CrM in the muscles indicate that both protocols illicit the same response at 28 days (9), and a loading phase is not required (33). Furthermore, some studies have used this protocol with creatine supplementation and reported increased cognitive function (27, 34). Our reason for choosing 5 g/day over 7 weeks was to increase compliance and decrease the risk of discomfort with high CrM intake. An intake five times a day for the first week is demanding and would likely result in some participants quitting the study.

At the mid-phase of the study, all baseline measurements will be repeated. The length of the intervention is 7 weeks. After the 7 weeks, all baseline measurements will be repeated (see Table 1). One week after last ingestion, the measurements will be performed one last time. At the week 8 appointment, every participant will be asked whether they thought they had received a placebo or CrM to determine how large an effect the placebo will have on the results.

**Table 1 tab1:** Study timeline.

	Pre (−1 week)			Intervention (7 weeks)			Post (+1 week)		
	CG	PLA	INT	CG	PLA	INT	CG	PLA	INT
Declaration of consent	X	X	X						
Height (m)	X	X	X				X	X	X
Weight (kg)	X	X	X	X	X	X	X	X	X
Concussion history	X	X	X						
Training status (hours/week)	X	X	X				X	X	X
RPQ (35, 36)	X	X	X	X	X	X	X	X	X
CrM						X			
Placebo powder					X				
Usual treatment				X	X	X			

CG will receive standard care. However, to our knowledge there is no commonly accepted description of standard care for PPCS in the literature. In general, these participants will be advised to continue with daily regular routines during the 7 weeks.

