## Methods and analysis

### Study design

The pilot study will be performed as a randomised controlled trial in accordance with the SPIRIT guidelines (30). The study will include a convenience sample of 45 patients. The patients will be randomly allocated to either a control group (CG), placebo group (PLA), or intervention group (INT), with 15 patients in each group. As there has been too few randomised controlled trials (RCT) to establish a sample size through power calculations, this pilot study will be used to establish a sample size for a future RCT.

The study will be double blinded, that is, the participants, staff and investigators, will be unaware of treatment group the patients are allocated to. Furthermore, the process of randomisation will consist of a nutritionist not otherwise associated with the study who will randomly allocate each participant to a group until the desired sample size is reached. The nutritionist in charge of this step will also distribute either the placebo or the CrM to the participants in each of these groups.

CG will not receive any treatment other than usual treatment. PLA and INT will both receive a powder that must be ingested. PLA will receive a powder similar in appearance to CrM, but with no apparent nutritional value. INT will receive CrM.

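### The week-8 allocation guess is meant to size the placebo effect, which it cannot do; read literally, it is also put to a control group that took neither powder.

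*Protocol article*

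**What the plan says.** The Procedure section places the question at the last visit, in week 8, and states its purpose in the same sentence: "every participant will be asked whether they thought they had received a placebo or CrM to determine how large an effect the placebo will have". No other purpose is given, and no earlier guess is described.

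Study design sets up three randomised arms of 15: control (CG), placebo (PLA) and creatine (INT). On the powders it says that "PLA and INT will both receive a powder that must be ingested", and of the controls that "CG will not receive any treatment other than usual treatment". Table 1 agrees: the creatine row is marked only for INT and the placebo row only for PLA.

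The Statistics section names linear mixed regression for outcome differences between groups. It does not mention the guess.

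**The concern.** The purpose attached to the question does not match what the question measures. All 30 powder recipients took something, so all were exposed to whatever effect taking a powder has. Sorting them by what they believe compares one set of exposed people with another and includes no one who took nothing. The design does contain the comparison that bears on a placebo effect, PLA against CG, but the sentence assigns that job to the guess.

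The respondents are also wrong as written. The text says "every participant will be asked whether they thought they had received a placebo or CrM", and nothing excepts CG.

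What is at stake is a misread placebo effect. The pilot is meant to inform the sample size and methods of a later RCT, so a placebo effect that is invented or missed could carry into that design.

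**Working it through.** The plan gives no figure for this point, so there is none to reproduce. The arm sizes are consistent: 3 × 15 = 45.

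**1. Who is asked, and what could be true for them**

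| Arm | n | Took | Can either answer be true? |
|---|---|---|---|
| INT | 15 | creatine powder | yes |
| PLA | 15 | placebo powder | yes |
| CG | 15 | no powder | no |

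Read literally, 15/45 = 33% of respondents are offered two false answers. The remaining 30 are the only people the question concerns. A control participant also knows that no powder was taken, so the Study design statement that participants do not know their group cannot hold for CG.

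**2. What a guess contrast estimates**

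The natural way to turn the guess into an effect size is mean improvement among those who believe they took creatine, minus mean improvement among those who believe they took placebo, over PLA and INT. This was compared with PLA minus CG in a simulation (20,000 runs, 15 per arm, improvement in SD units). The assumptions are mine, not the plan's.

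(a) No placebo effect and no creatine effect. The probability of guessing creatine is 1/(1 + exp(−b × own improvement)).

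| Slope b per SD | Guess contrast (SD) | PLA − CG (SD) |
|---|---|---|
| 0 | 0.00 | 0.00 |
| 0.5 | 0.47 | 0.00 |
| 1 | 0.83 | 0.00 |
| 2 | 1.21 | 0.00 |

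(b) True placebo effect of 0.5 SD in both powder arms, guess made at random.

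| Guess contrast (SD) | PLA − CG (SD) |
|---|---|
| 0.00 | 0.50 |

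The guess can show an effect that is absent and miss one that is present. PLA − CG is right on average in both cases.

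**3. How precise the proper contrast is**

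For two arms of 15 with a common SD, the 95% half-width is t(28) × SD × √(1/15 + 1/15) = 2.048 × √(2/15) × SD = 2.048 × 0.365 × SD ≈ 0.75 SD. This is a simple two-sample calculation with all 30 participants retained. Dropout would widen it, and use of baseline and repeated measures in the mixed model could narrow it.

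**4. Timing**

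The mid-phase measurement comes first ("At the mid-phase of the study, all baseline measurements will be repeated"), then another at the end of the 7 weeks, then the final one: "One week after last ingestion, the measurements will be performed one last time". The guess falls at about the time of that final set. RPQ is self-reported, so participants know their own course when they guess. The order of RPQ and guess within the visit is not given.

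**The case against.** The strongest reply is that this is one descriptive question at the last visit of a small pilot, loosely worded, with no analysis attached. Much of that stands, and several stronger readings go beyond the document.

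- A reader might infer that the trial will report a guess-based placebo effect or adjust RPQ for the guess. The Statistics section plans neither. The error lies in the stated purpose and would do harm only if someone acted on it.
- A reader might infer that the plan overlooks PLA against CG. It does not exclude it: mixed regression between three groups can deliver that contrast, and a fuller protocol or analysis plan may name it. Nor is the contrast clean. Controls know they took nothing and the outcome is self-reported, so it mixes placebo response with reporting bias.
- A reader might infer that outcomes will already have shaped the week-8 guess. That is a likely risk, but the document does not state it. A mid-phase guess would also follow weeks of experienced symptoms.
- A reader might infer that a third of the information is lost. CG answers can be set aside, leaving all 30 relevant ones. The wording may simply have meant every powder recipient, although it does not say so.
- A reader might argue that a late guess would make sound blinding look broken. Suppose 60% of INT and 40% of PLA improve and improvers guess creatine. Then 9 of 15 are correct in each arm, and the blinding index is 2 × 0.60 − 1 = 0.20. Its standard error is √(4 × 0.6 × 0.4/15) = 0.25, so the 95% interval is about −0.30 to 0.70. The exact two-sided p against 50% is about 0.61, and about 0.36 for 18 of 30 pooled. At this size the result could not be told from chance guessing.

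None of this rescues the stated purpose. It is written into the text, not a detail left to another document, and the literal wording does include CG.

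**Conclusion.** The point holds in a limited form. The Procedure section gives the allocation guess a purpose it cannot serve and, as written, puts the question to 15 people for whom neither answer is true. The mismatch of purpose and respondents follows from the text alone. The sizes (a spurious contrast of 0.47 to 1.21 SD, or a true 0.5 SD missed) rest on the assumed link between improvement and guessing and are illustrations, not forecasts. The ±0.75 SD assumes 15 analysed per arm and a common SD.

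The weight is modest. Allocation, the primary outcome and the planned between-group model are untouched, and the guess remains usable as a description of blinding in PLA and INT. It is still worth correcting, because the later RCT will draw on this pilot and the repair is nearly free.

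**What to change.** - In Procedure, replace the stated purpose. Say that the placebo effect is estimated by the randomised PLA − CG difference in RPQ change from the planned mixed model, with a 95% confidence interval. Add that CG knows it took no powder, and that 15 per arm gives a half-width of about 0.75 SD.
- Relabel the guess as a blinding check put to PLA and INT only and reported descriptively by arm, with the caveat that an answer given at week 8 may partly reflect perceived improvement.

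The cost is a few reworded sentences, with no new visit or measurement.

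Optional additions are to ask the question at mid-phase as well and to offer a don't-know answer. These add an item at an existing visit and a response option. Their small downside is that they may prompt participants to think about allocation. The correction does not depend on them.

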### Study timeline

Table 1.

### Participants and recruitment

The study population will be patients who have been experiencing PPCS for 6–12 months at start of participation. Participants will be recruited through social media and 14 neurological outpatient clinics in Denmark. At the start of the study, participants will be between 25 and 35 years of age. This will make the population homogenous regarding age, and we will avoid the physical and cognitive challenges associated with early childhood and adolescents (37–39), the degeneration in physical capacity that begins at approximately 35 years of age (39), and the cognitive decline that begins around the same time (40).

The anthropometrics of the participants will consist of age (years), gender (male/female), height (cm), body mass (kg), period with PPCS (months), and training status (hours/week).

### Inclusion criteria

Diagnosis of concussion/mild traumatic brain injury (1) from either the emergency care unit or general practitioner, with symptoms for a minimum of 6 months and a maximum of 12 months before the start of the inclusion.Age between 25 and 35 years.

### Exclusion criteria

Elite athletes and people who are normally physically active for more than 10 h a week on average.Participation in other interventions/treatments beyond this study.Pregnancy.Moderate or severe traumatic brain injury.Current intake of CrM.

### Outcomes

Primary

o PPCS will be measured using the Rivermead Post-Concussion Symptoms Questionnaire (RPQ). The RPQ is a questionnaire intended to quantify symptoms related to PPCS; it measures 16 commonly experienced symptoms following concussion. It is a comparison of pre-morbid levels with levels within the last 24 h (35). The patients will score each of the 16 symptoms from 0 (not experienced at all) to 4 (a severe problem). When all 16 symptoms are scored, the overall score is calculated by adding the scores together. A higher score is associated with a greater expected severity of PPCS (41). The first three questions concern (RPQ-3) the typical acute symptoms, while questions 4–16 (RPQ-13) concern the later symptoms manifesting after days or weeks (41).

Secondary

o TBI/concussion history will be assessed using the Ohio State tool, a self-report questionnaire regarding lifetime history of head and neck injuries.o Furthermore, we will monitor adverse events in line with general guidelines, even though we have found no evidence that CrM should have any adverse effects in the dose given (9).

### Potential confunders

Body weight will be measured at baseline, halfway through the intervention, and 1 week after the end of the intervention. These measurements are performed to ensure that changes in body weight do not affect the results, as changes in body weight are common with CrM supplementation.Physical activity will be self-reported in hours/week throughout the study period, as this can be a relevant factor to measure.

In the pilot study we will not assess the risk factors, but in the future RCT study, we will assess generally accepted risk factors.

### Statistics

Scales will be assessed for internal reliability, and Cronbach’s alpha will be estimated. We will apply unpaired t-tests to assess mean score differences at baseline and chi-square tests for sex distribution. Differences over time will be explored using paired sample t-tests. Applying Cohen’s d, effect sizes will be derived by calculating mean differences and standard deviations. To assess differences in outcomes between groups, we will employ linear mixed regression. All statistical analyses will be performed using SPSS for Windows (IBM Corp., 2018., Version 25.0., Armonk, NY).

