**Methods:**

The study is designed as a double-blinded randomised controlled trial. Study participants are found through neurological outpatient clinics in Denmark or through social media. They will be between 25 and 35 years of age, will have suffered from PPCS for 6–12 months prior to inclusion, and will have no comorbidities. The participants will be randomly allocated to either an intervention group (INT), placebo group (PLA), or control group (CG). Baseline data will be collected immediately after inclusion, and the study period will be 7 weeks. Follow-up data will be collected 1 week after the end of the study period. The primary outcome of the study is changes in RPQ score. Changes in weight and training status will be adjusted for as potential confounders.

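### Baseline differences are to be significance-tested, while baseline RPQ is not named among the adjustment variables for a change-in-RPQ outcome

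*Protocol article*

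**What the plan says.** The Study design section describes a randomised three-arm pilot: "The study will include a convenience sample of 45 patients", "with 15 patients in each group". The Abstract (Methods) gives the outcome: "The primary outcome of the study is changes in RPQ score". Table 1 shows RPQ collected before, during and after the intervention in all three arms.

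The Statistics section gives three separate elements:

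- Baseline: "We will apply unpaired t-tests to assess mean score differences at baseline and chi-square tests for sex distribution".
- Within patients: "Differences over time will be explored using paired sample t-tests". Cohen's d is then to be computed from mean differences and standard deviations. The text does not say whether these are differences over time or between arms.
- Between arms: "To assess differences in outcomes between groups, we will employ linear mixed regression". No fixed effects are listed.

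On covariates, the Abstract says: "Changes in weight and training status will be adjusted for as potential confounders". The section on potential confounders discusses the same two variables, body weight and physical activity. Neither place mentions baseline RPQ.

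**The concern.** There are two linked problems.

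First, the baseline tests answer no useful question. If allocation was random, the null hypothesis of the test is true by design. What matters is how large the imbalance is and how strongly the variable predicts outcome, and a p-value reports neither. In arms of 15, a non-significant result can be mistaken for evidence of balance.

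Second, a patient's baseline score on a symptom scale usually predicts the later score. Here it is already collected, and it is part of the outcome's definition. The article names covariates but not this one. Subtracting baseline is not the same as adjusting for it: patients who start high tend to fall further through regression to the mean, so a chance difference between arms at baseline carries into the difference in mean change.

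The stake is the precision of the between-group estimate and its sensitivity to chance imbalance. This matters beyond the pilot because "this pilot study will be used to establish a sample size for a future RCT". If the pilot's effect size is used for that purpose, any shift in it is passed on.

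**Working it through.** **Inputs from the article.** Three arms of 15, and 3 × 15 = 45, which matches the stated total. There is no power statement to reproduce.

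**Assumptions not in the article.** Two-sided 5% tests; equal RPQ variance at baseline and follow-up; baseline-to-follow-up correlation rho of 0.5 to 0.8. The article gives no SD for RPQ, so results are in SD units.

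**1. What a baseline t-test can detect.** The standard error of the difference between two arm means is SD × √(2/15) = 0.365 SD. The two-sided 5% critical value of t on 28 degrees of freedom is 2.048. An observed difference is therefore significant only above 2.048 × 0.365 = 0.75 SD. An observed imbalance of 0.5 SD gives t = 0.5/0.365 = 1.37 and would be reported as non-significant.

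An unpaired t-test compares two groups, and the article does not say which pairs are meant. If all three pairs are tested, simulation gives at least one false positive per variable in about 12% of trials.

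**2. How often imbalance arises.** For one pair of arms, P(|difference| > 0.5 SD) = 2 × [1 − Φ(0.5/0.365)] = 2 × [1 − Φ(1.37)] = 0.17. By simulation, at least one of the three pairs differs by more than 0.5 SD in about 36% of trials.

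**3. Precision.** Relative to an unadjusted follow-up comparison, the variance factor is 2(1 − rho) for a change score and 1 − rho² for a baseline-adjusted comparison. Their ratio is (1 − rho²)/[2(1 − rho)] = (1 + rho)/2.

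| rho | change, 2(1−rho) | adjusted, 1−rho² | ratio | reciprocal | change-score n per arm to match 15 adjusted |
|---|---|---|---|---|---|
| 0.5 | 1.00 | 0.75 | 0.75 | 1.33 | 20.0 |
| 0.6 | 0.80 | 0.64 | 0.80 | 1.25 | 18.8 |
| 0.7 | 0.60 | 0.51 | 0.85 | 1.18 | 17.6 |
| 0.8 | 0.40 | 0.36 | 0.90 | 1.11 | 16.7 |

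**4. Does a mixed model settle the matter by itself?** I checked this with generalised least squares for four RPQ occasions (baseline, mid-phase, end of week 7, one week later), equal correlation between occasions and complete data. With baseline as a repeated response and arm means free at baseline, the group-by-time contrast has factor 2(1 − rho), the same as a change score. With a common baseline mean across arms it has factor 1 − rho², the same as covariate adjustment. The gain therefore depends on the specification, not on the choice of a mixed model.

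**5. Shift given an imbalance.** If two arms differ by 0.5 SD at baseline, the change-score contrast is displaced by (rho − 1) × 0.5 SD. This is −0.25, −0.20, −0.15 and −0.10 SD at rho of 0.5, 0.6, 0.7 and 0.8. The arm that starts worse appears to improve more. Linear adjustment for baseline removes this displacement.

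**The case against.** A reader might infer that the baseline tests take the place of adjustment, or that an unadjusted change-score analysis is planned. The document supports neither inference. The tests and the mixed regression are listed separately, and nothing says that a baseline p-value decides which covariates enter. The model's terms are not given. It could already carry baseline RPQ as a covariate or constrain the baseline means, and an article may leave such detail to a full protocol or analysis plan that is not shown. Naming change as the outcome does not exclude adjustment either: regressing change on baseline and arm gives the same arm effect as regressing follow-up on baseline and arm. The covariate sentence is one line of an abstract and need not be a complete list.

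The consequences are also bounded. This is a pilot with no power claim, so no stated target is missed. At rho of 0.8 the loss is about 1.7 patients per arm (16.7 against 15). Over repeated randomisations the change-score contrast is unbiased, so the shift in step 5 is conditional on the imbalance that occurred. Unpaired t-tests can be run pairwise, so having three arms does not by itself make them unusable.

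All of this stands and limits the claim. It does not rescue the baseline tests, which are written into the plan. Nor does naming a mixed model answer the question of baseline, as step 4 shows.

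**Conclusion.** The point holds in two parts of different strength.

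- **Unconditional:** significance tests of baseline differences are planned. They are uninformative after randomisation and, in arms of 15, cannot show balance, since the threshold is an observed difference of about 0.75 SD.
- **Conditional:** baseline RPQ is not named where other adjustment variables are. If the mixed regression analyses change without it, or uses an unconstrained group-by-time contrast, adjustment would cut the variance to 0.75 to 0.90 of its value, equivalent to about 33% down to 11% more patients. An imbalance above 0.5 SD between two given arms (probability 17%) would then move the estimate by at least 0.10 to 0.25 SD.

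The conditional figures rest on an assumed rho of 0.5 to 0.8 and equal variances. They also treat the baseline slope as known; estimating it costs one of the 45 − 3 = 42 between-patient degrees of freedom, which trims the gain slightly. The document does not establish that baseline RPQ is left out of the model, only that it is not named. This is an inexpensive improvement worth making, not a flaw that invalidates the trial.

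**What to change.** 1. Remove the baseline t-tests and chi-square tests. Present baseline RPQ, sex and the other baseline characteristics descriptively by arm.
2. Prespecify that the linear mixed regression contains group, time, group-by-time and baseline RPQ as a fixed covariate, or equivalently takes baseline as a response with a common mean across arms. Include it regardless of the imbalance observed.
3. Derive the between-group effect size from that model, so that the figure available for planning the later trial is baseline-adjusted. State the standard deviation used to standardise it.

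If an analysis plan outside the article already contains items 2 and 3, a sentence pointing to it is enough. The cost is a change of wording only: RPQ is already collected at baseline in every arm, and no visit, measurement or patient is added.
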